# *2.0 Objectives*

*2.1 Primary Objective*

To determine the safety and tolerability of AQ (three days) plus SP (one day), PQP (three days) plus SP (one day) and Artekin TM (PQP plus DHA) (3 days) when used for seasonal IPT in children.

*2.2 Secondary Objective*

To determine the efficacy of AQ (three days) plus SP (one day), PQP (three days) plus SP (one day) and Artekin TM (PQP plus DHA)(3 days) when used for seasonal IPT in children.

*3.0 Study design and methods*

*3.1 Study area*

The study will be based at the MRC Field Station in Basse in the Upper River Division (URD) of The Gambia. This is an area of savannah typical of much of sub-Sahelian Africa. Malaria transmission is seasonal, occurring mostly during the short rainy season (July - October), and is almost exclusively due to *P.* *falciparum*. *Anopheles gambiae* is the principal vector; the area has the highest entomological inoculation rate (EIR) in The Gambia (between 1 and 50 infective bites per person per year). The population has worked with the MRC for at least 20 years and cordial relations exist between the MRC and surrounding villages.

*3.2 Enumeration, recruitment and consent*

The study will be carried in collaboration with the National Malaria Control Programme and URD District Health Team and study children will be recruited from villages in the south bank of Upper River Division. During the preparatory phase of the study, the design and objectives of the study will be discussed extensively with the URD District Team and all health care providers working in the study area. The study team will visit all the villages in the study area to explain the objectives of the trial to village elders, opinion leaders and village health workers. This will be followed by village meetings, which the entire community will be invited to participate. During these meetings, agreement to participate in the study will be obtained from the villagers. In addition, parents or guardians of prospective study subjects in the right age group will be visited at home and they will be provided with flyers in English and the appropriate local language (Mandinka, Sarahule or Fula).

Written informed consent will be obtained from the parent(s) or guardian(s) before a child is enrolled in the study. Approximately 1400 children aged between 1 to 5 years will be screened, of whom 1009 volunteers who meet the enrolment criteria will be enrolled in the study to receive SP plus AQ, SP plus PQP or Artekin TM. Clinic forms will be prepared and filled in by the study physician at screening. Each form will contain the subject’s initials, information about the subject’s date of birth, compound number, date of screening visit, whether the subject was enrolled or not and, when applicable, reasons for exclusion from the study based on medical history or physical or laboratory screening examination. A screening list will be prepared by the investigators as part of the routine source documentation. After review of the medical history, physical examination and laboratory results, reasons for non-eligibility will be documented on the list. Any clinically relevant finding will be treated at the discretion of the investigator. On entry into the trial a detailed clinical history, drug history, family history, and information on bednet usage and net impregnation will be obtained. The study physician will examine the child, document nutritional status and record the findings in a case report form. A finger-prick baseline blood sample will be obtained for determination of haemoglobin concentration and thick blood film preparation**.** Other investigations such as chest x-ray and urine examinations will be carried out as clinically indicated.

*3.3 Inclusion criteria*

1. Age between 1 to 5 years at enrolment.
2. Informed consent obtained from parents or legal guardians.
3. No current participation in another malaria intervention trial.
4. Free of obvious health problems as established by medical history and clinical examination before entering into the study.
5. Available for the duration of the study.

#

# *3.4 Exclusion criteria*

1. Known allergy to any of the antimalarial drugs used in the trial and if this is unknown, then a history of allergic reaction to any drug.
2. Acute or chronic, clinically significant pulmonary, cardiovascular, hepatic or renal functional abnormality, as determined by physical examination or laboratory tests.

*3.5 Withdrawal during the study*

***Withdrawal Criteria***

Study subjects may be withdrawn from the study for any one of the following reasons.

1. Withdrawal of parental / legal guardian’s consent.
2. Serious adverse event attributable to the study drug.
3. Loss to follow-up.

Children who develop adverse events attributable to study drugs should not receive further doses but should be followed-up to monitor safety up until the resolution of the adverse reaction.

*3.6 Randomisation*

Open-label, individual randomisation is proposed and will be done approximately three weeks before the first dose of IPTc administration planned for early September 2007. Study subjects will be individually randomised into either the AQ plus SP, PQP plus SP or ArtekinTM treatment groups in a 1:1:1 fashion. An independent statistician will generate the randomizing subject study number (SSN) that associates each SSN either to AQ plus SP, PQP plus SP or Artekin TM treatment groups and study subjects will be given treatment according to their randomisation group. A photo ID card will be given to all participants to facilitate identification at every contact, at home or in the health centres.

*3.7 Drug distribution at the health centres*

Study subjects and their parents will be informed about the date of treatment approximately one week before any intervention. Treatment will be given during the months of September, October and November. Drugs will be given at the nearest health centre by a designated member of staff. Tablets will be crushed, mixed with honey or suspended in water and given on a spoon. Staff who administer drugs at the health centre will play no further part in the trial. All participants will be kept under observation for 30 minutes after drugs are taken. In case of vomiting, the drug will be re-administrated. At the time of each monthly drug administration, a brief clinical assessment will be carried out. Children who are febrile will be screened for malaria using a rapid antigen test. Children found to have malaria will be treated with Lumefantrine-artemether (CoartemTM, Norvatis Pharma., Basel Switzerland).

*3.8 Treatment*

SP (tablets containing 500 mg sulfadoxine/ 25 mg pyrimethamine) will be given at an approximate dose of 1.25 mg pyrimethamine/25 mg sulfadoxine per kg stat.

Amodiaquine (200 mg base tablets) will be given at an approximate dose of 25 mg/kg over 3 days ( 10mg/kg D1, 10mg/kg D2 and 5mg/g D3).

PQ tablets (containing 320 mg per tablet) will be given at a target dose of 16.8 gm/kg once daily for 3 days.

Artekin *™* tablets tablet containing 40 mg of DHA and 320 mg PQ; Holleykin Pharmaceutical Co. Ltd., Guangzhou, China) will be used. Children will be given a dose of approximately PQP-DHA 1.6 / 12.8 mg/kg respectively. The drug will be given once daily for 3 days.

Coartem (tablet containing 20 mg artemether and 120 mg lumefantrine) will be given at the following doses: < 15kg: one tablet at the time of diagnosis, and then at 8, 24 and 48 hours.16-25kg : Two tablets as a single dose at the time of diagnosis, and then at 8, 24 and 48 hours.

*3.9 Assessment of adverse events*

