Piperaquine (PQP) is an orally active bisquinoline developed for clinical use in China in 1973(Wang et al., 1981, Yin et al., 1981, Yang et al., 1992, Lan et al., 1989, Chen et al., 1981, Shen et al., 1981). The phosphate salt is water-soluble. *In-vitro* testing in several laboratories has shown that PQP is approximately equivalent to CQ against sensitive parasites and significantly more effective than CQ against resistant *P.falciparum.* Like other members of this class of antimalarials, PQP chemically inhibits haem bio-crystallisation. The estimated terminal elimination half-life is approximately 17 days, but only limited pharmacokinetic (PK) data are available in man (Hung et al., 2003). The gastrointestinal side effects of PQP are similar to those of chloroquine but milder at total doses of less than 2g. Otherwise the toxicity profile is similar. PQP replaced CQ as recommended treatment for *falciparum* malaria in China in 1978. Over the next 14 years, 214 tons of PQP equivalent to 140,000,000 adult doses, were used for mass prophylaxis and treatment. Thus, in terms of drug treatment administered, PQP is amongst the most widely used antimalarial drugs in the world. Surveillance at the time found no adverse events other than rare cases of rash.

Dihydroartemisinin

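### Section 3.8, the protocol's only mg/kg dosing text, misprints one study-drug dose in each randomised arm: piperaquine (unit), Artekin (labels swapped) and amodiaquine day 3 (unit)

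*Protocol*

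**What the plan says.** All of the following stands in Protocol section 3.8 (Treatment), unless noted.

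- Piperaquine, for the PQP plus SP arm: "PQ tablets (containing 320 mg per tablet) will be given at a target dose of 16.8 gm/kg once daily for 3 days".
- Artekin: the product is described as a "tablet containing 40 mg of DHA and 320 mg PQ", and the dose follows as "Children will be given a dose of approximately PQP-DHA 1.6 / 12.8 mg/kg respectively".
- Amodiaquine, for the AQ plus SP arm: it "will be given at an approximate dose of 25 mg/kg over 3 days", in 200 mg base tablets. The daily split starts at 10 mg/kg on day 1 and continues "10mg/kg D2 and 5mg/g D3".
- SP: 25 mg/kg sulfadoxine with 1.25 mg/kg pyrimethamine, from a 500 mg / 25 mg tablet.
- Coartem, for children found to have malaria: it "will be given at the following doses: < 15kg: one tablet at the time of diagnosis"; the next band is "16-25kg : Two tablets as a single dose at the time of diagnosis".

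The piperaquine background in section 1.2.4 says that gastrointestinal side effects are "milder at total doses of less than 2g". The objectives in section 2 give only the number of treatment days per drug. No other section states a weight-based dose of a study drug.

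**The concern.** These are operative dosing instructions for children aged 1 to 5 years, whose tablets are crushed and given by health-centre staff (section 3.7). The primary endpoint is the incidence of adverse events (section 3.12), so dose is the exposure that the trial compares. As printed, each of the three arms contains one drug whose dose is wrong. The piperaquine and amodiaquine lines carry an impossible unit. The Artekin line attaches each number to the wrong component, and the word that closes that sentence fixes the order, so it cannot be read leniently. With no second statement of the doses, staff would have to infer the right value.

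**Working it through.** **Inputs.** Doses and tablet strengths are those of section 3.8. The protocol gives no body weights, so 10 kg is assumed for illustration, with 8 to 20 kg as the range. Tablets per day = dose per kg × weight ÷ tablet strength.

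**A line that is right.** SP: the dose ratio is 25 ÷ 1.25 = 20 and the tablet ratio is 500 ÷ 25 = 20. They agree, so the section can be checked in this way.

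**Piperaquine.**
- As printed: 16.8 g/kg × 10 kg = 168 g a day; 168,000 mg ÷ 320 mg = 525 tablets a day (420 at 8 kg, 1,050 at 20 kg).
- With mg/kg: 168 mg a day; 168 ÷ 320 = 0.525 tablet (0.42 to 1.05 over 8 to 20 kg).
- The unit is therefore wrong by a factor of 1,000.
- The check fixes the unit but not the number. Over three days, 16.8 mg/kg gives 50.4 mg/kg, or 0.50 g at 10 kg and 1.01 g at 20 kg. The 12.8 mg/kg of piperaquine in Artekin gives 38.4 mg/kg, or 0.38 g and 0.77 g. Both lie under the 2 g of section 1.2.4. The two daily doses differ by 16.8 ÷ 12.8 = 1.31, and nothing in the text says whether that is intended.

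**Artekin.**
- Tablet, PQ:DHA = 320:40 = 8:1. Dose as printed, PQP:DHA = 1.6:12.8 = 1:8. No number of tablets meets both figures.
- Labels swapped, DHA 1.6 and PQP 12.8 mg/kg: 12.8 ÷ 1.6 = 8, as in the tablet. At 10 kg, DHA gives 16 ÷ 40 = 0.4 tablet and PQP gives 128 ÷ 320 = 0.4 tablet, an exact match.
- Each printed figure followed alone, at 10 kg:

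| Figure used | Tablets a day | Against 0.4 |
|---|---|---|
| DHA 12.8 mg/kg | 128 ÷ 40 = 3.2 | 8 times too much |
| PQP 1.6 mg/kg | 16 ÷ 320 = 0.05 | one eighth |

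- On the DHA figure, piperaquine would be 3.2 × 320 = 1,024 mg a day and 3,072 mg over three days, above the 2 g of section 1.2.4.

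**Amodiaquine.**
- With mg/kg throughout: 10 + 10 + 5 = 25 mg/kg, which reproduces the stated total.
- As printed: 5 mg/g = 5,000 mg/kg, so the total would be 10 + 10 + 5,000 = 5,020 mg/kg. At 10 kg, day 3 would be 50,000 ÷ 200 = 250 tablets.

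**Coartem (minor).** Taken literally, the bands end below 15 kg and resume at 16 kg, which leaves 15 to under 16 kg without a dose. If the sign stood for up to and including 15, the bands meet in whole kilograms.

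**The case against.** The strongest reply is that these are typing slips with little practical risk. Nobody can give 525 tablets of piperaquine or 250 of amodiaquine. The amodiaquine line is corrected by the total in its own sentence, and Artekin is a fixed combination whose component ratio cannot be misdelivered. No calculation in the protocol depends on these figures.

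Most of this stands. A reader might infer that children could receive thousand-fold overdoses; the document does not support that, because the printed amounts are physically absurd and would be noticed. A reader might also infer damage to the design or the power; there is none. The reply is weaker for Artekin. The fixed ratio prevents a wrong ratio but not a wrong tablet count, and 3.2 tablets a day can be given.

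Two further limits are fair. It is tempting to say that the piperaquine dose is certainly 16.8 mg/kg, but the tablet strength and section 1.2.4 settle only the unit. It is also tempting to list the Coartem bands as a fourth error. The comparison sign may have been altered when the text was extracted: section 3.10 has visibly lost the sign before 37.5°C in two places. The section does not say whether weights are recorded with decimals, and Coartem is malaria treatment, not a randomised regimen. The bands therefore deserve a question, not a finding.

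Extraction is a less likely explanation for the other three. They involve ordinary letters and word order, and nothing in the text points to an artefact, although one cannot be fully excluded for the two units.

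**Conclusion.** Three study-drug doses in section 3.8 are wrong as written, and the protocol's own text shows it: piperaquine and amodiaquine day 3 by a unit factor of 1,000, and Artekin by swapped labels that reverse an 8:1 ratio. The Artekin and amodiaquine corrections follow exactly from the tablet content and the stated total. For piperaquine only the unit follows; the number 16.8 needs confirmation.

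The Artekin line carries the most practical risk, since either printed figure followed alone gives an eight-fold over- or underdose at any weight. The tablet counts rest on assumed weights, but the ratios do not. The correction should be made because these are the only paediatric dosing instructions in a trial whose primary endpoint is adverse events. It leaves the design, sample size and planned comparisons untouched.

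**What to change.** In section 3.8:

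1. Change the piperaquine unit to mg/kg. Confirm that 16.8 mg/kg is the intended dose, given 12.8 mg/kg piperaquine in the Artekin arm, and if so say that the difference is deliberate.
2. Write the Artekin dose as DHA 1.6 / PQP 12.8 mg/kg.
3. Change amodiaquine day 3 to 5 mg/kg.
4. As a minor check, confirm that the Coartem bands are contiguous and take the cut-point from the drug label.

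The cost is one corrected paragraph, one confirmation of the piperaquine dose and one look at the Coartem label.

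### Section 3.8 states the piperaquine target dose in grams per kilogram, and nothing else in the protocol lets a reader verify the figure

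*Protocol*

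**What the plan says.** All trial-drug dose amounts stand in Protocol section 3.8 (Treatment). Section 2.1 repeats only the number of treatment days.

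- **Piperaquine, in the PQP plus SP arm:** "PQ tablets (containing 320 mg per tablet) will be given at a target dose of 16.8 gm/kg once daily for 3 days". No 3-day total is given.
- **Amodiaquine, in the AQ plus SP arm:** "Amodiaquine (200 mg base tablets) will be given at an approximate dose of 25 mg/kg over 3 days", split as "10mg/kg D1, 10mg/kg D2 and 5mg/g D3".
- **Artekin arm:** each "tablet containing 40 mg of DHA and 320 mg PQ", and "Children will be given a dose of approximately PQP-DHA 1.6 / 12.8 mg/kg respectively", once daily for 3 days.

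The SP dose, the first two amodiaquine doses and the Artekin dose are all in mg per kg. In the background, the piperaquine paragraph of section 1.2.4 describes gastrointestinal effects as similar to those of chloroquine but "milder at total doses of less than 2g". No other part of the protocol corrects or restates the piperaquine or the amodiaquine entry.

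**The concern.** The dose is the exposure whose safety this trial measures. The participants are children aged 1 to 5 years, and the primary endpoint in section 3.12.1 is the incidence of any adverse event. Section 3.14 builds the sample size on two comparisons, each alternative regimen against SP/AQ.

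A piperaquine dose in grams per kilogram is plainly not usable, so anyone who applies section 3.8 has to repair it. The difficulty is that the protocol offers nothing to check the repair against: no piperaquine total is stated, and the one other piperaquine dose carries a different figure and is itself mislabelled. Different readers could repair the entry differently and leave no record. It would then be unclear which dose the adverse-event results for that arm describe.

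**Working it through.** **Inputs.** From section 3.8: piperaquine 16.8 g/kg daily for 3 days in 320 mg tablets; amodiaquine 10 mg/kg, 10 mg/kg and 5 mg/g in 200 mg tablets, with a stated total of 25 mg/kg; Artekin 1.6 / 12.8 mg/kg with tablets of 40 mg DHA and 320 mg piperaquine. From section 1.2.4: total piperaquine doses below 2 g. The protocol gives no weight distribution. I assume 10 kg, with a range of 8 to 25 kg guided by the rescue-drug weight bands in section 3.8 (the lower band starts "< 15kg: one tablet at the time of diagnosis"; the upper ends at 25 kg).

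**1. The one stated total that can be checked (amodiaquine).**
- As written, 5 mg/g = 5 × 1000 = 5000 mg/kg, so the sum is 10 + 10 + 5000 = 5020 mg/kg. The stated 25 mg/kg is not reproduced.
- If all three entries share the unit mg/kg, 10 + 10 + 5 = 25 mg/kg and the stated total is reproduced.
- Literal day-3 dose at 10 kg: 5 mg/g × 10,000 g = 50 g; 50,000 / 200 = 250 tablets (200 to 625 over 8 to 25 kg).

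**2. Piperaquine as written.** Tablets per day = dose per kg × weight / tablet strength.

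| Assumed weight | Dose per day | 320 mg tablets per day | Tablets over 3 days |
|---|---|---|---|
| 8 kg | 134.4 g | 420 | 1260 |
| 10 kg | 168 g | 525 | 1575 |
| 25 kg | 420 g | 1312.5 | 3937.5 |

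At 10 kg the 3-day total is 3 × 168 = 504 g. Against the 2 g mentioned in section 1.2.4, that is 504 / 2 = 252 times as much. The 2 g is background on tolerability, not a trial limit; it only shows the scale on which the protocol itself discusses the drug.

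**3. Can the figure 16.8 be confirmed from the Artekin line?**
- Tablet ratio DHA to piperaquine: 40 / 320 = 0.125. Dose ratio: 1.6 / 12.8 = 0.125. The two figures fit the tablet as a pair.
- The label puts PQP first, so read literally it assigns 1.6 to piperaquine and 12.8 to DHA, the reverse of the tablet contents.
- Ignoring units, 16.8 / 12.8 = 1.31 if piperaquine is the larger Artekin figure, and 16.8 / 1.6 = 10.5 if the label is followed. Neither gives 1.

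So correcting only the unit would still leave two different piperaquine figures in two arms, with no explanation, and an Artekin line that contradicts its own tablet.

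**4. Sample size.** 286 × 3 / (1 − 0.15) = 1009.4, which reproduces the stated 1009. No dose enters section 3.14.

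**The case against.** The strongest objection is that these are clerical slips that expose themselves. Much of it stands.

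- **Amodiaquine.** A reader might infer that two of the three regimens are equally unusable. They are not: the total and the first two daily doses in the same sentence leave one consistent reading of the third. This is a lesser slip.
- **Literal overdose.** A reader might infer that children would receive a thousandfold dose and that this would drive the primary comparison. The protocol does not support that. Section 3.7 has tablets crushed and given on a spoon, so hundreds of tablets a day could not be administered.
- **Route to the child.** One might assume that dosing sheets are copied from section 3.8. The protocol mentions no dosing sheets. Section 3.13 refers to SOPs for field and laboratory staff, which are not at hand, so how doses reach the health-centre staff is unknown.
- **Self-contradiction.** A 320 mg tablet does not strictly contradict a dose in grams per kilogram; it makes the tablet count absurd. The firmer evidence is the mg-per-kg unit used for the other weight-based doses in 3.8 and the 2 g scale in section 1.2.4.
- **Abbreviation.** Section 3.8 writes PQ where the protocol elsewhere uses PQP. No other drug in the document could be meant, so this is editorial.

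What the objection does not remove is the piperaquine entry. That its unit is implausible is obvious; what it should say instead is not verifiable from the text. The Artekin order and the 16.8 against 12.8 discrepancy are not self-evidently impossible, and could pass unnoticed.

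**Conclusion.** The point holds, chiefly for piperaquine. The operative dosing section states a dose that cannot be given as written, by a margin of hundreds of tablets a day (525 at 10 kg; 420 to about 1313 over 8 to 25 kg), and the protocol contains no total or second source that would confirm the number. The Artekin line adds a component order that conflicts with its tablet contents. The day-3 amodiaquine unit is wrong but resolved within its own sentence.

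The realistic consequence is an undocumented or inconsistent correction in a paediatric safety trial, not literal administration. The documents do not allow the size of that risk to be estimated. Sample size and power do not change. The tablet counts rest on assumed weights; the unit conflict, the amodiaquine sum (5020 against 25 mg/kg) and the Artekin ratio do not. Because the entry defines a randomised regimen, it must be corrected before dosing.

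**What to change.** By amendment before the first dosing round, the sponsor should reconcile within section 3.8, and with section 1.2.4:

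1. the piperaquine unit and figure;
2. the day-3 amodiaquine unit with the stated 3-day total;
3. the order of the Artekin components with the tablet contents;
4. the two piperaquine figures, 16.8 and 12.8, by either explaining or reconciling the difference between arms.

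The sponsor's pharmacist and physician should confirm every figure, and any SOP or other working document that carries the doses should be checked against the amended text. No dose is proposed here.

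The cost is one wording amendment plus that confirmation. The correction in itself calls for no change to the sample size, the endpoints or the visit schedule.

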Dihydroartemisinin-piperaquine (DP) is an artemisinin-containing, fixed-combination antimalarial drug developed in China. It has been evaluated extensively in clinical trials in Thailand, Vietnam, Cambodia, and China (Denis et al., 2002, Tran et al., 2004, Guo, 1993). Efficacy has been high and tolerability uniformly excellent in all trials in these multi-drug resistant areas including Cambodia and Vietnam (Denis et al., 2002, Tran et al., 2004), where PQP-resistance was common after extensive use. These trials have used a constant dose of PQP, but initially the co-formulation also included trimethoprim (CV8). This formulation (CV8) has been used extensively in Vietnam, where it is part of national policy. More recently the dose of DHA in DHA-PQP has been increased by 25%. This product (ArtekinTM) has been registered in China, Cambodia and Vietnam and in several countries in Africa including Senegal. DP is being used increasingly in Southeast Asia and is already part of national treatment recommendations in Cambodia and Vietnam. An alternative formulation of Artekin TM is being developed by the Medicines for malaria venture and should be ready for licensure in 2008.

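### The Artekin dose line in Protocol section 3.8 has its two component labels the wrong way round, so no number of the stated tablets can deliver the dose as written

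*Protocol*

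**What the plan says.** Protocol section 3.8 (Treatment) names the product and its strength: "tablets tablet containing 40 mg of DHA and 320 mg PQ". It then sets the weight-based dose: "Children will be given a dose of approximately PQP-DHA 1.6 / 12.8 mg/kg respectively". The schedule follows: "The drug will be given once daily for 3 days".

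The background (section 1.2.4, under ArtekinTM) describes the product in these terms: "Dihydroartemisinin-piperaquine (DP) is an artemisinin-containing, fixed-combination antimalarial drug developed in China". The ratio of the two components is therefore set by the tablet and cannot be varied at the point of dosing.

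No other line in the protocol gives an Artekin dose per kg. The only other piperaquine dose is in the line above, for the piperaquine plus SP arm: "PQ tablets (containing 320 mg per tablet) will be given at a target dose of 16.8 gm/kg once daily for 3 days".

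**The concern.** The last word of the dose sentence ties the first figure to PQP and the second to DHA. That makes DHA the larger component by a factor of eight, whereas the tablet described one sentence earlier contains eight times as much piperaquine as DHA. The two statements cannot both be right.

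This line is the only dose instruction for one of the three arms, and the children are aged 1 to 5 years. Section 3.7 has tablets crushed and given by spoon at health centres, so someone has to turn the mg/kg figures into parts of a tablet. Safety and tolerability are the primary objective (section 2.1), so the dose given is the exposure under test.

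**Working it through.** **Inputs (Protocol section 3.8)**

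- Tablet: 40 mg DHA and 320 mg piperaquine. The protocol uses PQ and PQP interchangeably.
- Dose as written: PQP 1.6 mg/kg, DHA 12.8 mg/kg.
- Body weights are not given in the protocol. Those used below are assumptions (8 to 20 kg). The results per kg do not depend on them.

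**1. Ratio check**

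- Tablet, piperaquine to DHA: 320/40 = 8.
- Dose line as written, PQP to DHA: 1.6/12.8 = 0.125.
- Dose line with labels exchanged: 12.8/1.6 = 8, which matches the tablet.

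**2. Tablets per kg** (dose per kg divided by tablet content)

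| Reading | From DHA | From PQP |
|---|---|---|
| As written | 12.8/40 = 0.32 | 1.6/320 = 0.005 |
| Labels exchanged | 1.6/40 = 0.04 | 12.8/320 = 0.04 |

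As written, the two components call for different tablet counts. With the labels exchanged they agree exactly.

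**3. Consequence of a literal conversion, against 0.04 tablets/kg**

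- Dosing from the DHA figure: 0.32/0.04 = 8 times the consistent dose. Piperaquine received would be 0.32 × 320 = 102.4 mg/kg a day instead of 12.8.
- Dosing from the PQP figure: 0.005/0.04 = 0.125, one eighth of the consistent dose. DHA received would be 0.005 × 40 = 0.2 mg/kg a day instead of 1.6.

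**4. Tablets a day at assumed weights**

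| Weight (kg) | Labels exchanged | Literal, from DHA | Literal, from PQP |
|---|---|---|---|
| 8 | 0.32 | 2.56 | 0.04 |
| 10 | 0.4 | 3.2 | 0.05 |
| 12.5 | 0.5 | 4.0 | 0.0625 |
| 15 | 0.6 | 4.8 | 0.075 |
| 20 | 0.8 | 6.4 | 0.1 |

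**5. Comparison with neighbouring lines**

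The SP line in the same section passes the same test. Pyrimethamine 1.25/25 = 0.05 and sulfadoxine 25/500 = 0.05 tablets/kg, so both components agree.

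The piperaquine-alone line gives only weak support. As printed, in grams, it would need 16,800/320 = 52.5 tablets/kg. If milligrams are meant (an assumption), it is 16.8/320 = 0.0525 tablets/kg. That is the same order as 12.8/320 = 0.04 and far from 1.6/320 = 0.005, which suggests that 12.8 is the piperaquine figure. Because that line has a unit error of its own, the conclusion here rests on the tablet ratio and not on it.

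**The case against.** The strongest reply is that this is a slip in label order which the adjacent sentence resolves. Both numbers, the tablet strength and the schedule are usable, and swapping two labels restores full agreement without any outside source. The harmful readings also look implausible in practice. One would give a 10 kg child 3.2 tablets a day, and the other would require 0.05 of a tablet, which could hardly be measured out. Either should prompt a query. Dosing sheets and procedures are not in the document, so it is not known whether anyone would dose from this line. Endpoints, analysis population and power do not depend on it. The unit in the piperaquine-alone line is a separate defect in another arm and should add no weight.

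Most of this stands. The 8-fold and one-eighth figures describe a literal misreading and do not predict what would happen, and there is no statistical consequence. The reply does not remove the error, however. The word approximately in the dose line cannot cover a reversed ratio, nor could a salt or base distinction between PQ and PQP plausibly do so. The protocol has no second statement of the dose to fall back on, and it describes no safeguard on dose conversion.

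**Conclusion.** The concern holds. As written, the Artekin dose cannot be given with the stated tablet. The labels are transposed and the numbers themselves are right: DHA 1.6 mg/kg and PQP 12.8 mg/kg each correspond to 0.04 tablets/kg. A literal conversion from a single component would be wrong by a factor of 8, upwards or downwards depending on which component is used.

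The conclusion assumes only that the stated tablet strength is correct and that PQ and PQP mean the same component. Body weights affect only the illustrative tablet counts. It should be fixed because it is the sole dose instruction for a paediatric arm in a safety trial. It does not rank higher because the intended dose can be recovered from the text and the sample size and analysis are unaffected.

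**What to change.** Replace the dose line with: DHA 1.6 mg/kg and PQP 12.8 mg/kg, given once a day for three days. Adding the equivalent of 0.04 tablets/kg would give dosing staff a direct check. The sponsor's pharmacist and physician should confirm the line before dosing sheets are made.

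At the same pass, check two separate unit slips in section 3.8: the piperaquine-alone dose, printed in grams per kg, and the amodiaquine day 3 dose, printed per gram.

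The cost is a one-line correction by amendment, with no effect on sample size, analysis or timelines.

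### Section 3.8 misprints a dose in each arm: the Artekin component labels are reversed (an 8-fold error either way), and piperaquine and amodiaquine day 3 carry impossible units

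*Protocol*

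**What the plan says.** Protocol Section 3.8 (Treatment) sets the doses for all three arms.

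- **Artekin arm.** The product is a "tablet containing 40 mg of DHA and 320 mg PQ". The dose follows: "Children will be given a dose of approximately PQP-DHA 1.6 / 12.8 mg/kg respectively", once daily for 3 days.
- **Piperaquine plus SP arm.** "PQ tablets (containing 320 mg per tablet) will be given at a target dose of 16.8 gm/kg once daily for 3 days".
- **Amodiaquine plus SP arm.** "Amodiaquine (200 mg base tablets) will be given at an approximate dose of 25 mg/kg over 3 days", split as "10mg/kg D1, 10mg/kg D2 and 5mg/g D3".

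No other section of the protocol states these doses or corrects them. Section 2.1 gives only the number of days for each drug.

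**The concern.** Each of the three lines conflicts with a figure beside it. The Artekin line gives the smaller dose to the component that makes up most of the tablet. The piperaquine line is in grams per kilogram although the tablets hold 320 mg. The amodiaquine line changes unit on day 3, so its parts no longer add up to the stated total.

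The lines differ in what is at stake. The two unit slips give doses that nobody could administer, so they mainly need proofreading. The Artekin line can be carried out as printed, because a few tablets a day looks like a plausible instruction. The children are aged 1 to 5 years and free of obvious health problems, the treatment is preventive, and the primary endpoint (Section 3.12.1) is the incidence of adverse events, which depends on dose. Section 3.8 gives the rescue drug, Coartem, as tablets by weight band. Artekin is given only in mg/kg, so someone has to convert it.

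**Working it through.** **Inputs, all from Section 3.8.** Artekin tablet: 40 mg DHA and 320 mg piperaquine. Printed Artekin pair: piperaquine 1.6 and DHA 12.8 mg/kg. Piperaquine tablet: 320 mg; printed target 16.8 g/kg. Amodiaquine tablet: 200 mg; stated total 25 mg/kg; printed split 10 mg/kg, 10 mg/kg, 5 mg/g.

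**Assumption.** The protocol gives no body weights. I use 8 to 20 kg for illustration. The 8-, 64- and 1000-fold ratios do not depend on it.

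**Does the method pass a correct line?** For SP, the tablet ratio is 500/25 = 20 and the dose ratio is 25/1.25 = 20. They agree.

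**Artekin, ratio.** Tablet, piperaquine to DHA: 320/40 = 8. As printed: 1.6/12.8 = 0.125. With labels exchanged: 12.8/1.6 = 8. Only the exchanged labels fit.

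**Artekin, tablets.** Tablets per kg = dose in mg/kg divided by mg per tablet.

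| Dosed from | Tablets per kg per day | DHA, mg/kg | Piperaquine, mg/kg | Tablets per day, 8 to 20 kg | Relative to intended |
|---|---|---|---|---|---|
| Exchanged labels (either component) | 1.6/40 = 12.8/320 = 0.04 | 1.6 | 12.8 | 0.32 to 0.80 | 1 |
| Printed DHA figure | 12.8/40 = 0.32 | 12.8 | 102.4 | 2.56 to 6.4 | 8 |
| Printed piperaquine figure | 1.6/320 = 0.005 | 0.2 | 1.6 | 0.04 to 0.10 | 1/8 |

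The two printed figures imply tablet counts that differ by 0.32/0.005 = 64-fold.

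**Piperaquine per 3-day Artekin round.** Intended: 0.32 × 320 × 3 = 307.2 mg to 0.80 × 320 × 3 = 768 mg. From the printed DHA figure: 2.56 × 320 × 3 = 2,457.6 mg to 6.4 × 320 × 3 = 6,144 mg. For orientation only, Section 1.2.4 calls the gastrointestinal effects of piperaquine "similar to those of chloroquine but milder at total doses of less than 2g"; it gives no age for that threshold.

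**Piperaquine with SP.** As printed: 16,800/320 = 52.5 tablets per kg, or 420 to 1,050 tablets a day. In mg/kg: 16.8/320 = 0.0525 tablet per kg, or 0.42 to 1.05 tablets a day. The ratio is 1000.

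**Amodiaquine day 3.** The stated total is reproduced only in mg/kg: 10 + 10 + 5 = 25. As printed, 5 mg/g = 5,000 mg/kg and the sum is 5,020 mg/kg. In tablets, day 3 would be 5,000 × 8/200 = 200 to 5,000 × 20/200 = 500, against 0.2 to 0.5 at 5 mg/kg.

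**The case against.** The strongest reply is that these are copy-editing errors which the text itself corrects. A reader sees at once that gm/kg and mg/g are slips. The Artekin tablet content stands just before the reversed pair, and piperaquine alone is given a figure of 16.8 in the preceding lines, so 1.6 for piperaquine looks odd. Harm would require someone to dose from one component, take its label literally and ignore the tablet content. Drugs are given by designated health-centre staff, and Section 3.13 mentions Standard Operating Procedures, which may hold a correct dosing chart. Nothing in the design, sample size or planned comparisons with SP/AQ changes.

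Much of this stands. The unit slips are minor, the intended Artekin dose can be recovered, and anyone who uses both printed figures will notice the conflict. The order in which the product is named is also no evidence: Section 1.2.4 writes DHA-PQP, while Section 2.1 writes PQP plus DHA. Only the tablet ratio settles the matter.

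What does not stand is leaving the text as it is. Any dosing chart has to be drawn from Section 3.8 or checked against it. The procedures are not shown, and Section 3.13 mentions them for field and laboratory staff in the context of data collection. The reversed line is the one error of the three that could be followed without looking absurd.

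**Conclusion.** All three lines are wrong as written, and the protocol's own figures show it. The Artekin reversal is the one of substance: 8 times both components if dosed from the printed DHA figure, one eighth if dosed from the printed piperaquine figure. These factors rest only on the stated tablet content; tablet counts rest on the assumed 8 to 20 kg. The risk depends on someone using one figure alone, and nothing shows that this would happen. The two 1000-fold unit errors are proofreading matters. Once the lines are corrected, the planned comparisons are unaffected. The protocol should be corrected, because this is its only dosing text and the participants are young children.

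**What to change.** Correct three lines of Section 3.8 before the first treatment round:

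1. Artekin: label the pair DHA-PQP, 1.6 / 12.8 mg/kg, so that DHA is 1.6 and piperaquine 12.8.
2. Piperaquine with SP: change the unit from gm/kg to mg/kg.
3. Amodiaquine day 3: change 5 mg/g to 5 mg/kg.

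The cost is one protocol correction, with no extra data, visits or sample size.

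A separate query, held with low confidence and not part of this finding: the sponsor could confirm that 16.8 mg/kg a day of piperaquine with SP, against 12.8 mg/kg a day in Artekin, is intended, and that both refer to the same form of the drug, since the section uses both PQ and PQP. The protocol does not require the two doses to match.
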